#### Secondary research questions and hypotheses

RQ 2.Are there any improvements in other clinical signs of CRPS, psychological functioning, and neuropsychological symptoms following PA treatment?

In addition to the primary outcome measures of pain and CRPS symptom severity, we aim to evaluate the effects of PA treatment on secondary outcomes (listed below) that are relevant to participants’ daily physical and psychological functioning, and for understanding the mechanisms of the therapeutic effects of PA (e.g., through establishing which neuropsychological symptoms might be affected by treatment).

Hypothesis: Compared to the sham treatment group, participants in the PA group will have a reduction in spatial attention bias (consistent with its primary applications), as well as bias in cognitive representation of space and spatially-modulated motor function; body representation distortion (see [22]); emotional disturbance; fear of movement; average pain, movement restriction, and symptoms interference; and sensory, motor, and autonomic signs of CRPS following treatment.
RQ 3.How long are any benefits sustained for after the cessation of PA treatment?

We will determine this through assessment of all primary and secondary outcomes immediately and 4 weeks after the completion of treatment, and through additional assessment of a subset of self-reported secondary outcomes at 3 and 6 months post-treatment. The time course of any improvements will be also analysed at more granular level through participants’ daily subjective ratings of pain, range of movement, and the extent to which their symptoms interfere with daily life over a period of 10 weeks.
RQ 4.Are there factors that can predict the CRPS progression over time and/or the response to PA treatment?

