Finally, the current study aims to explore potential predictors of the course of the disease and therapeutic response by tracking the symptoms of the same individuals over the course of 7.5 months. We plan to identify possible markers that would account for the individual differences in the progression of CRPS over time and / or in response to PA treatment. Due to insufficient evidence to support any specific predictions and limited sample size, we will perform exploratory analyses to address this research question. Factors such as demographic characteristics, pain intensity, CRPS symptom severity, sensory, motor and autonomic functions, and the extent of neuropsychological changes will be taken into consideration.
RQ 5.Are the neuropsychological changes in CRPS related to clinical signs and symptoms of CRPS?

A secondary aim of this study is to investigate the relationships between the severity of clinical symptoms of CRPS and the extent of neuropsychological changes in spatial attention, space and body representations, and motor functions.

Hypothesis: Baseline abnormalities in perception of and attention to the affected limb and its surrounding space in participants with CRPS (compared to the perception and attention of healthy control participants) will correlate with the severity of pre-treatment clinical symptoms.

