### Measurements

Tests and measures used in the current study and time points at which they are administered are listed in Table 3. These are categorised as self-report questionnaires, clinical assessments, or computer-based tests.

**Table 3 Tab3:** Measures

Measurement domain	Measurement tool	Time points	Research question^a^/justification for use
Self-report measures			
Pain and symptom interference	Current pain intensity (Item 6 of the Brief Pain Inventory)	Weeks 1, 4, 7, 11, 19 & 31	RQ1, RQ3, RQ4, RQ5; group matching on baseline pain
	Brief Pain Inventory^b^ (BPI; short form; pain intensity and interference) [42]		RQ2, RQ3, RQ4, RQ5
	Pain Detect Questionnaire [43]		RQ2, RQ3, RQ4, RQ5
	Average pain intensity (Logbook)	Weeks 1 to 11 (daily)	RQ2, RQ3
	Average symptom interference (Logbook)		RQ2, RQ3
Physical functioning	Average range of movement (Logbook)	Weeks 1 to 11 (daily)	RQ2, RQ3
	Edinburgh Handedness Inventory (current and change) [44]	Week 1	RQ4, RQ5; participant characteristics
Body representation	Bath CRPS Body Perception Disturbance Scale (BPDS) [45]	Weeks 1, 4, 7, 11, 19 & 31	RQ2, RQ3, RQ4, RQ5
Emotional functioning	Tampa Scale for Kinesiophobia^b^ [46]	Weeks 1, 4, 7, 11, 19 & 31	RQ2, RQ3, RQ4, RQ5; group matching on baseline fear of movement
	Profile of Mood States [47]		RQ2, RQ3, RQ4, RQ5; group matching on baseline mood disturbance
	Revised Life Orientation Test [48]	Week 1	RQ4; group matching on baseline levels of optimism
Treatment expectations	Patient-Centred Outcomes Questionnaire [49]	Week 1	RQ4; group matching on expectations of treatment outcomes
Impression of treatment outcome	Patient’s Global Impression of Change [50]	Weeks 7, 11, 19 & 31	RQ2, RQ3
Treatment adherence	Treatment sessions (Logbook)	Weeks 4 to 6 (twice-daily)	Monitoring treatment adherence
Clinical assessments			
CRPS diagnosis	Budapest diagnostic research criteria assessment [51]	Weeks 1, 4, 7 & 11	Verification of CRPS diagnosis and assessment of eligibility
Symptom severity	CRPS severity score [52]	Weeks 1, 4, 7 & 11	RQ1, RQ3, RQ4, RQ5; group matching on baseline symptom severity
Autonomic functions	Limb temperature asymmetry	Weeks 1, 4, 7 & 11	RQ2, RQ3, RQ4, RQ5
	Oedema		
Motor functions	Grip strength	Weeks 1, 4, 7 & 11	RQ2, RQ3, RQ4, RQ5
	Δ Finger-To-Palm distance (ΔFTP)		
Sensory functions	Mechanical Detection Threshold (MDT)	Weeks 1, 4, 7 & 11	RQ2, RQ3, RQ4, RQ5
	Mechanical Pain Threshold (MPT)		
	Mechanical Allodynia		
	Two-Point Discrimination [53]		

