#### Predictors of the response to PA treatment and/or CRPS progression over time (RQ4)

We will conduct exploratory analyses of the potential factors that can predict response to treatment for the PA group. First, we will calculate reduction scores as a change in current pain scores and CRPS severity scores from the immediate pre-treatment to immediate post-treatment sessions (RS3 – RS2). Second, we will conduct two separate linear mixed models regressions on pain reduction scores and CRPS severity reduction scores including the pertinent explanatory factors such as demographic characteristics; current pain intensity; CRPS severity score; and scores on the self-report questionnaires, clinical assessments, and computer-based tests. In the first instance, we will consider those outcomes that differed the most from the healthy control participants in RS1 (see statistical analyses for RQ5 in the next section).

The same factors will be considered potential explanatory variables in linear mixed models regressions on current pain scores and CRPS severity scores across four research sessions (RS1-RS4). These exploratory analyses will be conducted for data from all the participants with CRPS to examine possible predictors of CRPS progression over time (including but not limited to treatment group).

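### RQ4 promises predictors of CRPS course over 7.5 months, but its progression models stop at RS4 (10 of 30 weeks), leaving the week 19 and 31 pain scores unused for this exploratory aim

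*Protocol article*

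**What the plan says.** Under Secondary research questions and hypotheses, RQ4 asks: "Are there factors that can predict the CRPS progression over time and/or the response to PA treatment". The paragraph that follows says predictors of disease course and response will be explored by "tracking the symptoms of the same individuals over the course of 7.5 months". It gives the question exploratory status: "we will perform exploratory analyses to address this research question".

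In Table 3 (Measurements), current pain intensity is scheduled at "Weeks 1, 4, 7, 11, 19 & 31", and RQ4 is one of the research questions listed for that row. The CRPS severity score is scheduled at weeks 1, 4, 7 and 11 only.

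The analysis section for RQ4 has two parts:

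- **Response models**, in the PA group, on change "from the immediate pre-treatment to immediate post-treatment sessions (RS3 – RS2".
- **Progression models**, in all participants with CRPS: "linear mixed models regressions on current pain scores and CRPS severity scores across four research sessions (RS1-RS4". Their purpose is "to examine possible predictors of CRPS progression over time (including but not limited to treatment group".

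The late pain scores are used elsewhere. The RQ1 analysis of pain is a 2 × 6 ANOVA that includes LTFU1 and LTFU2. The Timing section schedules an analysis of current pain once all participants reach LTFU2, but does not link it to RQ4.

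**The concern.** The objective and the analysis name different periods. The objective spans RS1 to LTFU2; the analysis fixes RS1 to RS4. Because the shorter window is stated outright, this is not a detail that a condensed article leaves to a fuller plan.

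The RS1-RS4 window consists of a four-week baseline, two weeks of treatment and the four weeks after it. The protocol itself expects participants to drift back to their pre-treatment level over time; that is its reason for carrying RS2 forward. Some of the change within this window may therefore be a passing response to two weeks of PA or sham treatment. How much is not known from the document. Weeks 11 to 31 are the part of follow-up best placed to separate a lasting course from such a response, and they are left out. A report that labelled the RS1-RS4 results as predictors of CRPS progression would claim more than the model can show.

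**Working it through.** **1. The plan's own span.** RS1 is week 1 and LTFU2 is week 31 (Design). 31 − 1 = 30 weeks, and 30 / 4 = 7.5 months at four weeks per month, so the stated 7.5 months is reproduced. In calendar months, 30 × 7 / 30.44 ≈ 6.9.

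**2. Coverage of the progression models.** RS1 to RS4 runs from week 1 to week 11, which is 10 weeks, or 10 / 30 = one third of the period in the objective. For current pain the model uses 4 of 6 scheduled assessments. With 42 participants that is 42 × 4 = 168 scores instead of 42 × 6 = 252, so up to 84 are unused for RQ4.

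**3. Does another passage close the gap?**

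| Place in the protocol article | Outcome time points | Answers RQ4? |
|---|---|---|
| RQ4 objective | 7.5 months | States the aim |
| RQ4 response models | RS2 to RS3 | Response only |
| RQ4 progression models | RS1-RS4 | Yes, for 10 weeks |
| RQ1 pain ANOVA | RS1-LTFU2 | No: tests group and time, not individual predictors |
| Timing, after LTFU2 | Includes LTFU1 and LTFU2 | Not linked to RQ4 |

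No row covers individual predictors beyond week 11.

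**4. What the two late scores could add: upper limit.** Assume a straight-line course, equal residual variance and no variation in slope between people. The residual variance of one person's slope is σ² / Sxx, where Sxx is the sum of squared deviations of the assessment weeks from their mean.

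- Weeks 1, 4, 7, 11: mean 5.75; Sxx = 22.5625 + 3.0625 + 1.5625 + 27.5625 = 54.75.
- Weeks 1, 4, 7, 11, 19, 31: mean 12.17; Sxx = 620.83.
- Ratio 620.83 / 54.75 = 11.3; √11.3 ≈ 3.4 in standard error.

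Coding the visits as elapsed weeks (0, 4, 6, 10, 18, 30) gives 605.33 / 52.0 = 11.6, and again about 3.4.

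**5. With variation in slopes between people.** The variance becomes τ² + σ² / Sxx. The document gives neither quantity. I assume σ = 1 point and show two values of τ.

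| τ (points/week) | Four time points | Six time points | SE ratio |
|---|---|---|---|
| 0 | 0.0183 | 0.0016 | 3.4 |
| 0.05 | 0.0025 + 0.0183 = 0.0208 | 0.0025 + 0.0016 = 0.0041 | 2.2 |
| 0.1 | 0.0100 + 0.0183 = 0.0283 | 0.0100 + 0.0016 = 0.0116 | 1.6 |

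A predictor analysis presumes τ > 0, so the lower rows are the more relevant. A non-linear course or missing postal returns would reduce the gain further.

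**The case against.** A reader might infer that the 3- and 6-month pain scores are thrown away. They are not. They enter the 2 × 6 ANOVA, and four of its eight contrasts per group involve LTFU1 or LTFU2. They are unused only for RQ4.

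A reader might also infer from Table 3 that weeks 19 and 31 were collected for RQ4. The table does not show this. It lists all weeks and all research questions for a measure in one row, and the same pain row names RQ5, which the footnote limits to week 1. The purpose the protocol gives for the late assessments is RQ3, how long benefit lasts. The mismatch therefore rests on the RQ4 objective paragraph, not on the table.

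There is a possible reason for stopping at RS4. Clinical assessments, computer-based tests and CRPS severity are candidate predictors, and all end at week 11. If predictors vary over time, RS1-RS4 is the only window in which they and pain are observed together. With baseline predictors the obstacle disappears. The analysis text does not say which is meant, so this objection shapes the fix but does not remove the point.

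Extension also has a difficulty. Replacement of withdrawn participants secures full datasets for RS1-RS4 only. The RS2-carried-forward rule is written for the ITT treatment outcome analyses. If it were also applied here, missing postal returns would enter as RS2 values at the weeks with most influence on a slope. This stands and must be dealt with.

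Finally, RQ4 is declared exploratory in a limited sample, and treatment group is already in the model. Both are correct and limit the weight of the point.

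**Conclusion.** The point holds as a mismatch between an exploratory objective and its analysis. RQ4 is framed over 7.5 months, its progression models cover 10 of 30 weeks, and nothing in the document reconciles the two. It bites for current pain, which is measured to week 31. The CRPS severity model already uses every visit at which severity is assessed, so there only the reach of the conclusion is at issue.

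The possible gain in the standard error of a pain slope is at most about 3.4-fold, under a linear course with no slope variation. It is about 1.6 to 2.2-fold under an assumed residual SD of 1 and slope SD of 0.1 to 0.05 points per week. It would be wrong to read the 11-fold variance ratio as the expected benefit: the plan specifies no linear slope and expects a return towards baseline. It would also be wrong to infer any effect on the RQ1 efficacy conclusions, since the RQ4 models play no part in them.

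**What to change.** In the RQ4 analysis section:

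- Fit the all-participant progression model for current pain on all six time points (RS1-LTFU2), once LTFU2 is complete.
- Use actual time since RS1, in a form that allows non-linear change, and keep treatment group in the model as already planned.
- Use RS1 values of the predictors.
- Use the observed scores under the mixed model, and state that RS2 is not carried forward for missing postal returns in this analysis.
- Keep the CRPS severity model on RS1-RS4, and limit its conclusion to the 10 weeks around treatment.

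If the authors prefer to keep both models at RS1-RS4, the RQ4 objective should be reworded to that period. At minimum the two passages must agree.

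The cost is wording and analysis time; no new data are needed. The pain model would wait for LTFU2, when an analysis of current pain is already scheduled. Some postal returns will be missing, and the mixed model then relies on the missing scores being explained by the observed data.

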#### Baseline neuropsychological symptoms and their relationships with the clinical symptoms of CRPS (RQ5)

We will conduct a series of contrasts to compare mean age, proportion of males and females, and proportion of left- and right-handed individuals between participants with CRPS in RS1 (total CRPS sample, regardless of subsequent treatment allocation) and healthy controls. Participants’ mean scores on self-report questionnaires and clinical assessments in RS1 will also be compared between the two groups. Specifically, we will conduct contrasts to compare participants with CRPS and healthy controls groups on the BPDS and Profile Of Mood States scores; the hand laterality indices (current for healthy controls, and handedness before CRPS for the participants with CRPS); limb temperature asymmetry and hands size difference (affected – unaffected), grip strength and ΔFTP ratios (affected/unaffected), MDT, MPT, two-point discrimination threshold ratios, and mean allodynia score on the affected side.

To test whether the participants with CRPS in RS1 show visuospatial attention bias compared to healthy controls, we will use four separate contrasts. Specifically, we will conduct four between-group comparisons of the following variables: PSSs in the TOJ task, PSEs in the Landmark task, attention bias scores in the Greyscales task, and bias scores in the MNLB task.

The Directional Hypokinesia task conditions performed with the affected and unaffected hand will be analyzed separately. After excluding incorrect and missed trials, we will use mean movement initiation times (MITs) and movement execution times (METs) for each combination of VF in which the target appeared and hand Starting Position to test if the participants with CRPS show signs of directional hypokinesia compared to the healthy controls. We will conduct two three-way ANOVAs on MITs for each hand with the following factors: Group (participants with CRPS, healthy controls), VF (affected, unaffected), and Starting Position (affected, central, unaffected). Significant interactions will be followed by four a-priori contrasts to test whether the participants with CRPS are slower to initiate movements toward the targets in their affected side of space (regardless of the direction of reaching movement required) and / or in the direction toward their affected side of space (regardless of the location of the target). Specifically, we will examine if participants with CRPS have slower MITs to the targets in the affected VF than in the unaffected VF; to the affected VF compared to healthy controls; to the affected VF from central compared to affected Starting Position; and to the affected VF from central Starting Position compared to healthy controls. Analogous analyses will be conducted on METs to test if participants with CRPS show signs of directional bradykinesia compared to healthy controls. We will also examine differences between Groups (participants with CRPS, healthy controls) on MITs and METs through separate contrasts for each index (A and B) of directional hypokinesia and bradykinesia. As further exploratory analyses we will examine how many participants with CRPS are impaired on both indices (A and B) of directional hypokinesia and bradykinesia by identifying which participants obtained positive A and B indices and by comparing each CPRS patient’s indices to the mean indices for healthy controls using Crawford t-tests [112].

To test for differences in body representation as measured by the Hand Laterality Recognition task between the participants with CRPS and healthy controls, we will conduct two three-way ANOVAS with the factors Group (participants with CRPS, healthy controls), depicted Hand (affected, unaffected), and VF (affected, unaffected) on accuracy rates and RTs to accurate responses. If there are significant three-way interactions, we will conduct a-priori contrasts to test whether the participants with CRPS are less accurate and/or slower in responding to: the depicted hands corresponding to their affected hand compared to those corresponding to their unaffected hand when the hands are presented in the affected VF; the affected hands presented in the affected VF compared to the unaffected VF; the affected hands compared to the unaffected hands; the affected hands presented in the affected VF compared to healthy controls; the affected hands compared to healthy controls; and the hands presented in the affected VF compared to healthy controls. If there is no effect of VF, we will only consider accuracy rates/RTs to recognize affected and unaffected hands averaged across both VFs in follow-up contrasts and any further correlation/regression analyses.

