Photographs of the dorsal and palmar surface of both hands and forearms are taken so that the presence of skin colour and trophic changes can be double-scored by a researcher who is not involved in data collection and who is blind to the time point at which the photographs were taken, to which limb is affected by CRPS, and to which group the participant is allocated. Video recordings of both limbs performing the movements of fist closure and opening, wrist flexion and extension, and radial and ulnar wrist deviation are taken so that the motor abnormalities can be double-scored according to the same protocol. We will use Cohen’s kappa statistic to report inter-rater agreement.

An infrared thermometer is used to measure temperature asymmetry. Temperature measurements are taken to the nearest 0.1 °C from the dorsal and palmar surface of both hands (over the thenar muscle) and the centre of the region of worst pain as indicated by the participant. An arithmetic mean of the 3 measurements on each limb is calculated. According to the Budapest diagnostic criteria [51], an absolute difference between the affected and unaffected side greater than 1 °C is classed as a temperature asymmetry. When available, thermal images of both limbs are additionally taken (camera FLIR T620 that is sensitive to changes in temperature as small as 0.04 °C).

Oedema is measured using the figure-of-eight procedure that uses a soft tape measure. The detailed protocol for hand and wrist size measurement is described elsewhere [73]. This measure has excellent intra- and interrater reliability and concurrent validity compared with water volumetry [74]. Hand size is calculated as an arithmetic mean of 3 measurements performed on each hand. Presence of asymmetric oedema is considered if the average measure taken from the CRPS-affected hand is at least 0.56 cm larger compared to the unaffected hand, which was suggested to be a clinically relevant difference in a previous study [75].

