#### Sample size and power calculation

The required sample size was calculated based on the primary outcome measure of self-reported pain [109]. A meta-analysis defined a clinically significant reduction in pain as a change of Δ = − 2 (on a scale of 0–10) [110]. The sample size required to detect a pain reduction of this magnitude between RS2 and RS3 was estimated. The risk of type I error was set at 5% and the risk of type II error was set at 10%, giving 90% power to detect a significant change in the pain. The standard deviation expected in the current study was estimated as 1.98 based on pain intensity ratings obtained by our group in recent research [8]. Given these parameters, a minimum of 42 participants with CRPS (21 per group) is required to evaluate the effects of the PA treatment on the primary outcome measure of pain. Taking into account an anticipated drop-out rate of 20%, up to 52 participants with CRPS will be enrolled in order to obtain a total of at least 21 complete datasets for RS1-RS4 per treatment group. To provide normative data, 21 healthy (pain-free) control participants will be recruited.

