#### Effects of PA treatment on neuropsychological changes and other secondary outcomes (RQ2) and time course of any improvements (RQ3)

To analyze between-group (PA treatment vs. sham treatment) differences on the secondary outcome measures (see Table 3) across four (RS1-RS4) or six (RS1-LTFU2) time points, we will conduct 2 × 4 or 2 × 6 ANOVAs as described for the analyses of the primary outcomes. Specifically, a 2 × 4 ANOVA will be run on each clinical assessment outcome (limb temperature asymmetry, hands size difference, grip strength and ΔFTP ratios, MDT, MPT, two-point discrimination threshold ratios, and allodynia) and mean group scores in the following computer-based measures: PSSs in the TOJ task, PSEs in the Landmark task, attention bias scores in the Greyscales task, and bias scores in the MNLB task. We will also use 2 × 4 ANOVAS to analyse between-group differences on indices A and B for the affected and unaffected hand performance in the Directional Hypokinesia task, as well as on hand laterality recognition accuracy and RTs indices in the Hand Laterality Recognition task across RS1-RS4. Separate 2 × 6 ANOVAs will be run on mean group scores on each of the self-reported questionnaire measures: pain intensity and interference components of the BPI, the Pain Detect Questionnaire, The BPDS, the Tampa Scale for Kinesiophobia, and the Profile of Mood States.

We will plot group means of daily ratings of average pain, range of movement, and interference over time and use contrasts to identify the time points of significant group differences. We will also identify for both groups and for each measure the average number of days to reach peak improvement from the start of treatment, and the average number of days from the peak improvement to return to baseline.

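### Limb temperature asymmetry appears to be analysed as a signed side difference although either direction counts as abnormal, so warm and cold limbs can offset each other in the group mean

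*Protocol article*

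**What the plan says.** Four places in the protocol article bear on this.

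- **Clinical assessments.** Temperature is averaged over three sites per limb. The sign is present when there is "an absolute difference between the affected and unaffected side greater than" 1 °C, so a warmer and a colder affected limb both count. Oedema is treated differently: it is present only when the affected hand is "at least 0.56 cm larger compared to the unaffected hand", which is one-directional.
- **RQ5 analysis (RS1, CRPS against controls).** The variables compared include "limb temperature asymmetry and hands size difference (affected – unaffected"), followed by grip strength and ΔFTP ratios marked as affected over unaffected.
- **RQ2/RQ3 analysis (treatment effect).** The plan says "a 2 × 4 ANOVA will be run on each clinical assessment outcome (limb temperature asymmetry, hands size difference" and further measures). No formula for temperature is given here, and no step takes an absolute value.
- **Secondary research questions and hypotheses.** The prediction for PA against sham includes a reduction in "sensory, motor, and autonomic signs of CRPS following treatment".

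**The concern.** Where abnormality can lie on either side of zero, improvement means moving towards zero from either side. On an affected-minus-unaffected score, a warm limb that cools gives a negative change and a cold limb that warms gives a positive one. Averaged over a group, these offset each other. The same happens to the level at RS1: a CRPS group in which every limb is clearly asymmetric can have a mean near zero, as healthy controls do.

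A signed score suits hand size, because oedema is defined in one direction. One bracketed formula seems to have been attached to two outcomes, and it fits only one of them.

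The effect may reach later analyses. The RQ4 section first considers as predictors the outcomes that differed most from controls at RS1. The section on relationships between neuropsychological changes and clinical symptoms depends on which outcomes differ significantly from controls. A null result produced by cancellation could keep temperature out of both.

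**Working it through.** **The plan's own figure.** The only calculated figure is the sample size for pain, described as "giving 90% power to detect a significant change in the pain". With a difference of 2, SD 1.98, two-sided α = 0.05 and 90% power, n per arm = 2 × (1.960 + 1.282)² × (1.98/2)² = 20.6, so 21 per arm and 42 in total. It reproduces. Only the 21 per arm is carried forward.

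**Size of the cancellation.** Let m be the mean size of the asymmetry, r the proportion by which PA reduces it (sham unchanged), and p the share of limbs in the less common direction.

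- Expected PA–sham difference in change on the signed score: r × m × (1 − 2p).
- Expected CRPS–control difference at RS1 on the signed score: m × (1 − 2p).

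The documents give none of m, r, p or the visit-to-visit noise, so all are assumptions. With m = 1.5 °C and r = 0.5, the treatment difference is 0.75 × (1 − 2p): 0.75, 0.60, 0.45, 0.30, 0.15 and 0.00 °C for p = 0, 10, 20, 30, 40 and 50%.

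**Treatment comparison by simulation.** There were 20,000 trials per setting and 21 per arm, with asymmetry SD 0.5 °C between people and a t-test on the RS2–RS3 change (a simplification of the 2 × 4 ANOVA). Entries are power.

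| Mean asymmetry, reduction, noise SD | Signed, p = 0 | Signed, p = 30% | Signed, p = 50% | Absolute, any p |
|---|---|---|---|---|
| 1.5 °C, 50%, 0.4 | 98% | 25% | 5% | 98% |
| 1.5 °C, 50%, 0.5 | 90% | 20% | 5% | 89–90% |
| 1.0 °C, 50%, 0.5 | 59% | 13% | 5% | 55–56% |
| 1.0 °C, 25%, 0.4 | 29% | 9% | 5% | 29% |
| 1.0 °C, 50%, 0.7 | 36% | 9% | 5% | 29–30% |
| 0.7 °C, 25%, 0.7 | 9% | 6% | 5% | 8% |

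**RS1 contrast by simulation.** 42 CRPS participants against 21 controls, mean asymmetry 1.5 °C (SD 0.5), noise 0.5 °C, controls centred on 0 with SD 0.5. Signed power is 100, 100, 94, 61, 19 and 5% for p = 0 to 50% in steps of 10. On the absolute score the difference is about 1.11 °C and power is about 100% throughout.

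**Reading.** With mixed directions the signed score loses most of whatever power is available. With all limbs in one direction it loses nothing and can be slightly better (36% against 29–30% in the noisiest 1.0 °C row).

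**The case against.** The strongest reply is textual. The minus sign is written only for the RS1 contrast with controls, where nothing normalises. The treatment section names the outcome without a formula. The bracket could also qualify hand size alone, and a condensed article may leave score derivation to a fuller document. This stands as far as certainty goes: use of the signed score in the 2 × 4 ANOVA is an inference. The signed reading of the RS1 contrast is still the more natural one, because the next bracket, affected over unaffected, plainly covers both items before it. On either reading the treatment section does not say which score is meant.

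A second reply is that the 1 °C rule defines a present/absent sign, and a continuous outcome may legitimately be formed differently. That is true in general. Here, though, the hypothesis is a reduction in that sign, and a signed mean does not measure it when directions mix.

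A third reply is that the loss depends on inputs the documents do not give. This stands in full. Eligibility sets no minimum temperature asymmetry, so 1.5 °C is only an assumption. In the least favourable setting neither score has useful power.

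Two stronger readings are tempting. A reader might infer that the treatment analysis is stated to be signed and will miss a real effect; the text does not say so, and the mix is unknown. A reader might also infer that the primary result is at risk. It is not: pain does not involve temperature, and the CRPS severity score uses present/absent items, with temperature judged by the direction-free threshold.

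**Conclusion.** The point holds in a limited form. The RS1 contrast is most naturally read as using a signed temperature difference, which conflicts with treating either direction as abnormal. The treatment ANOVA appears to inherit that score because nothing else is specified. The loss is conditional on warm and cold limbs both being present. Under the assumed inputs, with asymmetry 1.5 °C, a 50% reduction and noise 0.4 °C, treatment-comparison power falls from 98% to 25% at a 30:70 mix and to 5% at 50:50. With smaller asymmetry, a smaller effect or more noise, the absolute score's own power drops to as little as about 8%, so there is less to lose. One secondary outcome is affected, with possible knock-on effects on the exploratory RQ4 and RQ5 analyses. RQ1, both primary outcomes and the sample size are untouched. It is worth correcting because the change is small and the data are already collected.

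**What to change.** In the RQ2/RQ3 and RQ5 analysis sections, state that the analysed limb temperature variable is |affected − unaffected|. Keep the signed difference for hand size, where it matches the definition of oedema. Report the signed temperature difference descriptively by group and visit, so that the warm/cold mix is visible.

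The cost is one line of wording and no new measurements. There are three downsides. Measurement noise pushes an absolute score upward near zero, in controls as well, and makes it skewed; the BCa bootstrap intervals and the bootstrapped mixed models already in the Statistical analyses section can deal with the skew. If all limbs deviate one way, a few points of power may be lost (up to about 7 in the settings above). And the absolute score hides a limb that switches from warm to cold, which is a further reason to show the signed values.
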